**Figure 1 F1:**
[figure not shown]
Flow diagram of the study, ∗Data: arterial systolic, diastolic, and mean blood pressure, heart rate, and SpO_2_, T0 = pre-induction baseline, T3 = at second tidal volume, under mechanical ventilation after intubation, ABGA = arterial blood gas analysis, SpO_2_ = oxygen saturation, T1 = 2 minutes after preoxygenation, T2 = 5 minutes after preoxygenation.

#### Defined time points

2.3.4

T0: preinduction baselineT1: 2 minutes after preoxygenationT2: 5 minutes after preoxygenationT3: at the second tidal volume with mechanical ventilation after intubation

### Outcomes

2.4

The primary outcome is PaO_2_ at the predefined time points.

The secondary outcomes include patients’ discomfort, end-tidal oxygen saturation (EtO_2_) at T0 and T3, EtCO_2_ at T0 and T3, other data from ABGA (eg, PaCO_2_, pH, base excess, and HCO_3_), apnea time, SpO_2_, and other vital signs (heart rate, arterial blood pressure).

The tertiary outcomes include the patients’ upper airway condition including the modified Mallampati score, upper lip bite test, thyromental distances and the presence of a mass within the upper airway tract, indication for surgery, seniority of the anesthesiologist, the number of attempts at laryngoscopy, use of any rescue maneuvers, and performers’ (anesthesiologists) satisfaction.^[10,15]^ Apnea time is defined the period from the time of propofol injection till the tracheal tube is secured.

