## Introduction

1

Preoxygenation before tracheal intubation is usually achieved by delivering oxygen via a facemask before induction of anesthesia. This potentially prolongs the time available for securing the airway before hypoxemia to approximately 6 minutes.^[1–5]^ After the patient loses consciousness, manual ventilation is usually performed using a facemask, until the tracheal intubation is confirmed. This period can be prolonged if tracheal intubation is attempted multiple times. However, facemask ventilation has traditionally been avoided due to the risk of gastric gas insufflation, which leads to increased intragastric pressure, and increases the risk of pulmonary aspiration of the gastric content. Moreover, if difficult mask ventilation is anticipated, facemask ventilation may not be possible at all. Moreover, 6 minutes of hypoxemia without mask ventilation may be insufficient for intubation and may be catastrophic in patients with difficult intubation.

An ideal preoxygenation protocol should extend the apnea period safely during induction of general anesthesia is essential, to prevent life-threatening events. The high-flow nasal cannula (HFNC), such as the OptiFlow System (Thrive, Fisher & Paykel, Auckland, New Zealand), has the ability to deliver warm and humidified oxygen through a specially designed nasal cannula, which enables comfortable oxygen delivery at rates >70 L/min.^[3,6–8]^ Several studies have showed that nasal delivery of humidified oxygen to paralyzed and anesthetized patients maintains oxygenation and achieves acceptable carbon dioxide concentrations.^[1–3,6,9–13]^ The study protocol involves a single-center, single-blinded, prospective, randomized controlled, and superiority trial, to prove the hypothesis that an extended apneic period with preoxygenation via the HFNC could be more beneficial to patients undergoing general anesthesia during induction compared with preoxygenation with a simple mask.

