### Study setting

2.1

The study protocol follows the standard protocol items: recommendation for interventional trials (SPIRIT) guidelines for reporting protocol items for randomized controlled trials (RCTs).^[14]^ The process of recruiting and enrolling the study population began in May, 2019 and is currently in progress at Asan Medical Center. Asan Medical Center is a tertiary academic hospital in Korea. The aim of the study is to assess arterial oxygen partial pressure (PaO_2_) at defined time points during preoxygenation and to compare the 2 methods, that is, preoxygenation with high-flow heated and humidified nasal cannula and standard preoxygenation with oxygen insufflation via a facemask. Assessments will be performed at baseline, 2 and 5 minutes, and immediately after intubation for each patient. Outcome assessors include the same anesthesiologist, who cannot be blinded. However, statisticians responsible for the final analysis will be blinded.

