#### Common procedure applied to all subjects

2.3.3

Standard monitoring including pulse oximetry (SpO_2_), 3-lead electrocardiogram (EKG), and noninvasive blood pressure will be performed. After local anesthesia, the artery catheter will be inserted into the radial artery or dorsalis pedis artery, with simultaneously baseline ABGA (T0) monitoring. After recording the data from the ABGA and initial vital signs, preoxygenation for a given group will be performed for 5 minutes. Recording of ABGA and the vital signs will be performed at the predefined time points (T1 and T2), before anesthesia injection. Endotracheal intubation will be attempted about 2 minutes after injection of anesthetics and muscle relaxants. After confirming intubation, mechanical ventilation will be started, and the vital signs and last ABGA (T3) will be recorded. The flow diagram of all the study measures is shown in Fig. 1. If the saturation recorded by the pulse oximeter falls below 90% during the procedure, the trial will be stopped immediately. If a patient from group N experiences intolerable discomfort during the course of the trial, the flow rate will be reduced to an acceptable level and recorded. If a patient from group M experiences extreme frustration because of the tight mask, the fitting should be released slightly and record. If appropriate actions are taken for each patient and he/she does not cooperate, he/she will be excluded, even if he/she has consented to participating in the study.

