### Sample size and recruitment

2.5

To determine the sample size for the study, we used previously published data^[9]^ showing that 5 minutes of preoxygenation with HFNC achieved a median of 406 (Q2: 362; Q3: 446) mm Hg, and 5 minutes of facemask preoxygenation achieved a median PaO_2_ of 335 (Q2: 292; Q3: 389) mm Hg. Estimated mean (SD) PaO_2_ achieved with the HFNC and simple mask are 339 (82.3) mm Hg and 405 (71.3) mm Hg, respectively. This yielded a sample size of 23 participants per group, with alpha = 0.05 and power = 0.8.^[16]^ We need 26 participants per group (total 52), after accounting for 10% screen failure. We used a program called G∗Power Version 3.1.7 (Kiel University, Germany) to calculate the sample size.

Patients will be recruited on the day before surgery, once the surgery is planned and the date is scheduled. As soon as sufficient explanation is provided and consent for clinical trials is obtained, they will be assigned to a randomized trial group. After arriving at the operating room for surgery, a monitor for general anesthesia will be started and the clinical trial will be also initiated. There will be no additional visit dates for the participants, as the clinical trial will be terminated as soon as the induction of general anesthesia is completed. Efforts will be made to screen and select the appropriate participants for clinical trials, to recruit participants, and to meet the target sample size.

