### Data collection management and analysis

2.6

After the examiner or the person designated by the examiner receives approval from the institutional review board (IRB), the participants’ data will be collected. To obtain accurate data, the outcome assessors have been given sufficient training, before conducting the trial, and the case report form (CRF) includes pictures and examples for objective assessment of the airway. The collected data should be stored in the original locked location, and access to the data is available only to the responsible investigator and investigators authorized by him.

To compare data between the groups, the chi-square test or Fisher exact test will be used to assess categorical variables. Student *t* test or the Mann–Whitney *U* test will be used to analyze continuous variables, as appropriate. All data manipulations and statistical analyses will be performed using SPSS for Windows, version 21 (IBM Corp, Armonk, NY) and Stata software version 13.1 (StataCorp LP, College Station, TX). Statistical analysis for the missing data will be adjusted with an estimating equation or statistical model in the final analysis. A 2-tailed *P* value of <.05 will be considered to indicate a statistically significant difference.

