## Discussion

3

Preoxygenation with an HFNC during induction of general anesthesia has recently become an appealing option to anesthesiologists.^[3,6,9–12]^ This trial primarily aims to examine the trajectory of PaO_2_ levels during the whole preoxygenation procedure before and after intubation. We expect that the preoxygenation with HFNC will prove superior to the classical method with facemask, during the preinduction period of general anesthesia. To maintain the quality of this study and arrive at a reliable conclusion, the experimental design method and the research results will go through strict quality control. We will use the CONSORT checklist for the experimental design.^[17]^ The main strength of our protocol is that the study population consists of patients with head and neck cancer, who are more likely to have a difficult airway.

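### The primary outcome spans several PaO2 time points with none deciding, while the sample size covers only the 5-minute value (T2)

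*Protocol article*

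**What the plan says.** - **Primary outcome (section 2.4):** "The primary outcome is PaO_2_ at the predefined time points". No time point is singled out.
- **Time points:** section 2.3.4 defines T0 (baseline before induction), T1 (2 minutes), T2 (5 minutes) and T3 (second ventilator breath after intubation). Section 2.1 gives the same four: "Assessments will be performed at baseline, 2 and 5 minutes, and immediately after intubation for each patient". Section 2.3.3 uses the phrase for two of them: "Recording of ABGA and the vital signs will be performed at the predefined time points (T1 and T2), before anesthesia injection".
- **Sample size (section 2.5):** it rests on published values after 5 minutes of preoxygenation ("5 minutes of preoxygenation with HFNC achieved a median of 406" mm Hg), which is T2 (Figure 1: "T2 = 5 minutes after preoxygenation"). The result is 23 per group, raised to 26.
- **Analysis (section 2.6):** continuous variables are compared by a t test or Mann–Whitney test, and "A 2-tailed *P* value of <.05 will be considered to indicate a statistically significant difference". A statistical model is mentioned only for missing data.
- **Aims:** the Introduction calls this a superiority trial and frames the hypothesis as "an extended apneic period with preoxygenation via the HFNC could be more beneficial to patients undergoing general anesthesia during induction". The Discussion says "We expect that the preoxygenation with HFNC will prove superior to the classical method with facemask, during the preinduction period of general anesthesia", and describes the primary aim as the PaO2 trajectory before and after intubation.

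**The concern.** A superiority claim needs a stated deciding comparison. Here superiority could be claimed on T2, on T3, on any one of the time points, or only on all of them. Each rule has its own error rate and power, and only T2 alone corresponds to the sample size. Read literally, the primary outcome also includes T0, which precedes the intervention and cannot measure its effect.

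The time points answer different questions. T1 and T2 are drawn before anesthetic injection and reflect preoxygenation alone. T3 is drawn after intubation, so it also reflects the interval from injection to tube. If T2 and T3 disagree, nothing in the article says which one counts, and the choice could then be made after the results are known.

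**Working it through.** **1. Reproduce the planned size.** Inputs from section 2.5: means 339 and 405 mm Hg, SDs 82.3 and 71.3, alpha 0.05, power 0.8. The labels on the two means appear swapped between arms relative to the medians; this does not change the absolute difference.

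- Difference = 405 − 339 = 66 mm Hg
- Pooled SD = √((82.3² + 71.3²)/2) = √5928.5 = 77.0
- Standardized effect d = 66/77.0 = 0.857
- Two-sample t test (noncentral t), two-sided 0.05: 23 per group gives power 0.811
- Inflation: 23/0.9 = 25.6, so 26 per group

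Both stated figures reproduce. The 23 is the size for one test, at one time point, at the full 0.05.

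**2. Error rate and power under other rules.** The article gives no correlation between PaO2 values at different times, so four are assumed. Simulation: 400,000 trials, 23 per group, three equally correlated normal outcomes, a t test on each at two-sided 0.05. Power and disagreement assume d = 0.857 at every time point.

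| Quantity | Corr. 0 | 0.5 | 0.8 | 0.9 |
|---|---|---|---|---|
| False positive, any of T1–T3 | 14.3% | 12.6% | 9.9% | 8.4% |
| False positive, T1 or T2 only | 9.8% | 9.1% | 7.8% | 7.0% |
| Power, all of T1–T3 required | 53% | 63% | 70% | 73% |
| T2 and T3 disagree on significance | 31% | 22% | 14% | 10% |

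Checks at correlation 0:

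- Any of three: 1 − 0.95³ = 0.143
- Any of two: 1 − 0.95² = 0.0975
- All three: 0.811³ = 0.53
- Disagreement: 2 × 0.811 × 0.189 = 0.31

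For comparison, T2 alone has a 5% false-positive chance and 81% power.

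**3. Splitting alpha three ways.** Each test is at 0.05/3 = 0.0167. With 23 per group, power per test is 0.662. Reaching 80% needs 30 per group, and 30/0.9 = 33.3, so 34 per group (68 in total) against the planned 26 (52).

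**The case against.** The strongest reply is that section 2.5 already anchors the trial on T2, so moving the claim to T3 would visibly depart from the powered comparison. Alpha allocation is also often left to an analysis plan, which is not shown. Both points are fair, and the absence of an allocation in section 2.6 would not be a finding by itself. But section 2.4 does define the primary outcome, in terms broader than what was sized, and powering a trial on T2 does not make T2 primary.

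Several points of emphasis stand:

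- The two-time-point reading is the weaker one. The bracket in section 2.3.3 may only say which samples precede injection.
- Linking the aims to single time points is an inference. The preinduction period covers T1 as well as T2, and apnea time is a separate secondary outcome.
- Serial PaO2 values taken minutes apart in one patient are unlikely to be independent. The 0.8 and 0.9 columns are the more plausible, though they still give 8% to 10% against 5%.
- Those rates count errors in both directions. False claims favoring HFNC are about half: roughly 5.0% and 4.2% at correlations 0.8 and 0.9, against 2.5% for one test. The relative inflation is the same.
- Nothing in the article supports the same effect at T1 and T3, so the power and disagreement figures are illustrative.
- T2 and T3 could still disagree after the fix. What changes is that the deciding result is known in advance.

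A joint or repeated-measures test would suit the trajectory aim better, but it would have to be prespecified and the trial sized for it.

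**Conclusion.** The concern holds. The stated primary outcome covers several unranked time points, while the stated sample size covers one comparison at T2. No success rule, hierarchy, summary measure or joint test connects them.

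If any of the three post-baseline tests may carry the claim, the false-positive chance is about 8% to 10% at correlations of 0.9 to 0.8, and at most about 14%, rather than 5%. If all three are required, power falls below the planned 80% at every correlation examined. The correlations, and the equal effect behind the power figures, are assumptions. Since no rule is stated, the figures show what each possible rule would mean and do not predict which would be used. This should be corrected; it does not invalidate the design.

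**What to change.** Replace the primary outcome sentence in section 2.4 with:

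> The primary outcome is PaO2 at T2 (after 5 minutes of preoxygenation, before anesthetic injection), compared between groups at a two-sided significance level of 0.05. PaO2 at T1 and T3 are secondary outcomes that describe the trajectory; T3 compares the whole induction strategy and bears on the apnea hypothesis. T0 is a baseline value.

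The sample size stays at 23 (26) per group, and every blood gas sample is still drawn and reported. Recruitment began in May 2019 and the trial is approved and registered, so the change needs an ethics amendment, a registry update and a record that it was made before results were examined. The scientific cost is that T3, the sample closest to the apnea hypothesis, loses primary status, and the trajectory becomes a secondary description.

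### Section 2.4 lists as outcomes eight items that preoxygenation cannot change, and the only comparison rule in section 2.6 does not exempt them from testing

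*Protocol article*

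**What the plan says.** Section 2.4 (Outcomes) sets out three tiers. The secondary tier includes "end-tidal oxygen saturation (EtO_2_) at T0 and T3, EtCO_2_ at T0 and T3". The tertiary tier opens with "The tertiary outcomes include the patients’ upper airway condition including the modified Mallampati score, upper lip bite test, thyromental distances" and continues with "the presence of a mass within the upper airway tract, indication for surgery, seniority of the anesthesiologist, the number of attempts at laryngoscopy", then rescue maneuvers and the satisfaction of the anesthesiologist. Descriptors and genuine outcomes stand in the same lists, with nothing to separate them.

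The legend of Figure 1 gives "T0 = pre-induction baseline", and section 2.3.4 agrees. Section 2.3.3 fixes the order: "After recording the data from the ABGA and initial vital signs, preoxygenation for a given group will be performed for 5 minutes".

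Section 2.6 has one rule for comparisons: "To compare data between the groups, the chi-square test or Fisher exact test will be used to assess categorical variables". Continuous variables get a t test or a Mann–Whitney test, and significance is two-tailed P<.05. The only model mentioned there is for missing data.

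**The concern.** An outcome has to be something that treatment could affect. Thyromental distance, an airway mass, the reason for surgery and a gas value recorded before treatment do not meet that condition. For such patient-level items randomization makes the null hypothesis true, so any significant result is a false positive. Under the present labels it would be reported as a difference in an outcome.

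There is also a smaller, missed opportunity. Airway difficulty plausibly predicts how long intubation takes, and the T0 end-tidal values plausibly predict those at T3. Filed as outcomes, these variables are not available in their natural role as covariates.

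**Working it through.** **Group size.** The inputs are in section 2.5: means 339 and 405 mm Hg, SDs 82.3 and 71.3, two-sided alpha 0.05, power 0.80.
- Pooled SD = √[(82.3² + 71.3²)/2] = 77.0. Standardized difference = 66/77.0 = 0.857.
- A two-sided t test needs 22.37, so 23 per group. Then 23/0.90 = 25.6, so 26 per group and 52 in total.

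The plan's figures reproduce, and nothing below changes them.

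**Count of items that treatment cannot change.** From section 2.4:
- Tertiary: Mallampati score, upper lip bite test, thyromental distance, airway mass, surgical indication, anesthesiologist seniority (6).
- Secondary: EtO2 at T0 and EtCO2 at T0 (2).

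The total is 8. Seven are patient-level and predate treatment. Seniority belongs to the setting.

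**Chance of at least one spurious difference.** If k items are each tested at 0.05 and are independent (an assumption), the chance is 1 − 0.95^k.

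| k | chance of at least one |
|---|---|
| 4 | 18.5% |
| 5 | 22.6% |
| 6 | 26.5% |
| 7 | 30.2% |
| 8 | 33.7% |

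The expected number of false positives among eight is 8 × 0.05 = 0.40. The airway measures are likely to be correlated, so the effective number of tests is probably below eight.

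The table also assumes that each test has its full nominal size. Fisher's exact test, which section 2.6 names, does not. At 26 per arm its true size, computed by exact enumeration, is about 1.0% at a prevalence of 0.1 and between 2.3% and 2.8% at prevalences of 0.2 to 0.5. A binary item tested that way contributes little more than half of 5%, or less.

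**Chance imbalance at 26 per arm.** The SE of a standardized baseline difference is √(2/26) = 0.277, so 95% of imbalances lie within ±1.96 × 0.277 = ±0.54 SD.

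**What adjustment would gain.** With covariate–outcome correlation r, residual variance falls by r²: 9% at r = 0.3 and 25% at r = 0.5 (assumed values).

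An illustration for apnea time assumes that 30% of patients have a difficult airway, that difficulty adds 30, 45 or 60 s, and that the residual SD is 40 s. None of these figures is in the article.
- Unadjusted SE = √[2(40² + 0.21 × shift²)/26] = 11.7, 12.5 or 13.5 s.
- Adjusted SE ≈ √(2 × 40²/26) = 11.1 s, before a small allowance for estimating the covariate effect.
- Simulated power for a 25 s difference rises from 55%, 49% or 45% to 59%, 58% or 60%.

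The gain is modest at the low end of this range and useful at the high end.

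**The case against.** **Testing is inferred.** The sentence in section 2.6 only matches the type of test to the type of variable. It does not announce a test of each airway item, and section 2.4 may simply list everything recorded. The T0 and T3 pairing for end-tidal gases reads easily as a measurement schedule. This stands: a reader might infer that the article commits to testing all eight, and it does not. But the items are declared outcomes and the one comparison rule exempts nothing, so the text permits those tests.

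**Adjustment is a different matter.** A reader might infer that the mislabelling leaves apnea time and laryngoscopy attempts wrongly analysed. The article does not support that. Relabelling would not itself adjust anything, covariate choice may sit in a fuller document that is not shown, and randomization keeps the unadjusted tests valid. In the illustration above their overall type I error stays near 5%. One can obtain 9% to 17% by looking only at trials with an airway imbalance of 20 points or more, but such trials are about 9.5% of the total. That figure does not describe the plan's error rate.

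**Consequence.** The primary comparison is untouched, and many readers would recognise a difference in Mallampati score as baseline imbalance. Apnea time, defined in section 2.4 as running from propofol injection to a secured tube, measures how long intubation takes. It does not measure how long apnea is tolerated, so adjusting it would not make it a test of the extended-apnea hypothesis in the Introduction. All of this stands and limits the weight of the point. It does not make the labels right.

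**Conclusion.** The misclassification is an error in the text of section 2.4: eight items that preoxygenation cannot affect are named as outcomes. Its consequence is conditional. If all eight are tested as section 2.6 allows, the chance of at least one spurious outcome difference is about 34% under independence and full test size, about 19% with four effectively independent tests, and lower where Fisher's exact test is used.

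Seniority needs a separate caveat. The article does not say whether the operator is fixed before the allocation is known, so an imbalance there need not be pure chance.

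Covariate adjustment is a precision gain and not a correction of bias. The apnea-time figures rest on assumed values and are illustrative only. The sample size of 23, inflated to 26 per group, and the primary PaO2 comparison are unaffected.

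**What to change.** In section 2.4, move Mallampati score, upper lip bite test, thyromental distance, airway mass, surgical indication, anesthesiologist seniority and the T0 end-tidal values to baseline characteristics. Keep as secondary and tertiary outcomes only what follows treatment, including EtO2 and EtCO2 at T3, apnea time, laryngoscopy attempts, rescue maneuvers, discomfort and satisfaction.

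In section 2.6, state that baseline characteristics are described by arm without significance tests. In place of the plain two-sample tests, analyse EtO2 and EtCO2 at T3 adjusted for their T0 values, and apnea time adjusted for one or two prespecified pre-treatment airway variables (for example Mallampati 3–4 versus 1–2, and airway mass). Describe seniority only, unless the operator is fixed before allocation is revealed.

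The cost is rewording two sections and one or two degrees of freedom out of about 50 (52 − 2). The plan already lists every variable needed.
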